### Data collection methods

#### **
*Screening visit*
**

Following a discussion of the study, and the obtaining of informed consent, the study investigator will question the participant regarding ocular and medical history. Retinal photographs will be taken if they have not already been acquired, and repeated if image quality is insufficient to allow evaluation. The OCT and fundus photographs will be assessed to check for eligibility. The Van Herick angle of drainage will be measured, media clarity will be assessed for each eye and the lens graded according to the Lens Opacities Classification System III grading scale [46]. Visual acuity will be assessed in each eye using the ETDRS chart, following a brief refraction, if necessary. An abridged version of the Mini Mental State Examination will be used to assess for cognitive impairment (5 min; [7]).

Those still deemed eligible for inclusion in the study will also complete several questionnaires, through verbal interview with the investigator: visual function (VA LV VFQ-48) [44]; health-related quality of life (EQ-5D); sleep quality (PSQI) [47]; smoking history (pack years); vitamin supplementation; ethnic origin.

#### **
*Baseline assessment*
**

Optical coherence tomography images and fundus photographs obtained during the participant’s routine visit to the ranibizumab clinic will be obtained and analyzed to assess drusen volume and AMD grade, according to the AREDS simplified scale [45]. If the images are of insufficient quality, additional images will be captured.

The ETDRS visual acuity will be assessed in each eye. Chromatic thresholds will be measured for the eye with early AMD using the Colour Assessment and Diagnosis test [48] (City Occupational Ltd). Contrast thresholds to a 14 Hz flickering stimulus will be measured for the eye with early AMD using the procedure outlined by Dimitrov et al. [49]. The rate of parafoveal cone dark adaptation will be determined for the eye with early AMD using a psychophysical procedure described previously [50]. Thresholds will be determined using a psychophysical method, based on a ‘3 down, 1 up’ staircase paradigm [50]. An array of white light-emitting diodes behind a diffusing filter will be used to light-adapt photoreceptors in the central 43.6° of the test eye (the output of the white light-emitting diodes will be modified by a Lee filter, HT015, to provide a retinal illuminance of 5.20 log phot Td.s^-1^, providing a bleach of 85% cone photopigment and 74% rhodopsin). All light levels fall within the safety guidelines set out in British Standard BS EN 15004-2 (2007) [51]. There will be an initial training phase, of around 5 minutes, then the adapting light will be presented, and finally recovery of visual thresholds will be monitored for 25 minutes after exposure to the adapting light.

Those individuals who are assigned to the treatment group will then be given a light mask, and provided with written and oral instructions on its use. There will also be a reprise of the key information provided in the participant information letter about follow-up appointments. Participants will be given written copies to take home of the PSQI questionnaire that will be used in the monthly interview.

#### **
*Monthly assessment*
**

The investigator will access the OCT images and medical records of all participants after they have attended the ranibizumab clinic for each monthly follow-up appointment. This will allow measurement of drusen volume on a monthly basis, which will allow the final analysis to include an assessment of the time course of any therapeutic action. Additionally, reviewing medical records will facilitate monitoring of the conversion rate to advanced AMD in the control and intervention groups in the eye with early AMD at baseline, and of ranibizumab retreatment rates in the eye with nAMD, for adverse event reporting purposes.

Participants in both intervention groups will attend a short, monthly follow-up appointment following their routine ranibizumab clinic appointment, during which both groups will complete the PSQI sleep quality questionnaire. In addition, the treatment group will bring their mask along to each monthly visit to allow objective compliance data (nightly hours of use) to be exported from the device, retraining in mask use if required, functionality of the mask to be checked, masks to be replaced every 12 weeks, and a semistructured interview to be carried out to determine the acceptability of the intervention. These data will be used to address secondary objectives 2 and 3.

#### **
*Final (12-month) visit*
**

This visit will be the same as the baseline visit with the addition of a final semistructured interview assessing the acceptability of the intervention, and the questionnaires (PSQI, VA LV VFQ-48, Euroqol).

#### **
*Baseline cross-sectional study*
**

The 40 participants recruited only to the cross-sectional part of the study will undergo the tests outlined in the baseline assessment visit of the trial.

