**Methods/design:**

ALight is a Phase I/IIa, multicentre, randomized controlled trial. Sixty participants (55 to 88 years old) with early AMD in one eye and neovascular AMD (nAMD) in the fellow eye will be recruited from nAMD clinics. They will be randomized (in the ratio 1:1), either to receive the intervention or to be in the untreated control group, stratified according to risk of disease progression. An additional 40 participants with healthy retinal appearance, or early AMD only, will be recruited for a baseline cross-sectional analysis. The intervention is an eye mask that emits a dim green light to illuminate the retina through closed eyelids at night. This is designed to reduce the metabolic activity of the retina, thereby reducing the potential risk of hypoxia. Participants will wear the mask every night for 12 months. Ophthalmologists carrying out monthly assessments will be masked to the treatment group, but participants will be aware of their treatment group. The primary outcome measure is the proportion of people who show disease progression during the trial period in the eye with early AMD. A co-primary outcome measure is the rate of retinal adaptation. As this is a trial of a CE-marked device for an off-label indication, a further main aim of this trial is to assess safety of the mask in the cohort of participants with AMD.

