## Methods/design

### Trial objectives

The primary aim of this study is to collect preliminary Phase I/IIa proof-of-concept trial data from people with early AMD in one eye and advanced nAMD in the fellow eye, recruited from a hospital nAMD clinic, in order to assess the impact of low-level night-time light therapy, compared with no intervention, on disease progression in the eye with early AMD. A further main aim of this trial is to assess safety of the mask in the cohort of participants with AMD.

The secondary aims of the study are to:

1. Establish the effect of low-level night-time light therapy, compared with no-treatment control, on secondary outcome measures, including: change in drusen volume from baseline in the eye with early AMD; ranibizumab retreatment rates in the fellow eye with nAMD; progression of early AMD on the basis of change in functional outcome measures; change in health-related quality of life (assessed using the EuroQol EQ-5D instrument); change in self-reported visual function assessed using the 48-item Veterans Affairs Low-Vision Visual Functioning Questionnaire (VA LV VFQ-48).

2. Establish the acceptability of low-level night-time light therapy in people with AMD by monthly qualitative interviews.

3. Determine the effect of low-level night-time light therapy on sleep patterns by conducting the Pittsburgh Sleep Quality Index (PSQI) questionnaire every month with both intervention arms by interview with the study investigator.

4. Establish the relationship between baseline functional biomarker outcomes and the severity of AMD (assessed using the simplified Age-Related Eye Disease Scale (AREDS) and initial drusen volume).

5. Evaluate the ability of all clinical tests to act as prognostic biomarkers for AMD progression.

6. Evaluate the ability of all clinical tests to act as predictive biomarkers for low-level night-time light therapy in people with AMD.

7. Compare the sensitivity of all clinical tests to disease progression over 12 months.

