### Interventions

Participants allocated to the treatment group will be given a 12-weekly disposable light mask (Polyphotonix Medical, UK) that presents organic light-emitting diode illumination (peak output 502 nm) to both eyes, to be used overnight for 12 weeks. Light masks will be replaced every 12 weeks at the participant’s routine appointment at the nAMD clinic so that the total duration of mask usage is 12 months.

The mask provides a luminance of 75 photopic cd/m^2^. When adjusted for the spectral sensitivity of rod photoreceptors, this equates to 186 scotopic cd/m^2^ [35]. Light transmission by the human eyelid has been found to range between 0.3% and 2% for light in the region of 500 to 505 nm [36-38]. Under these conditions, the pupil diameter in people in the age group 60 to 85 years is approximately 4 mm [39]. This will result in a retinal illuminance in the order of 23 scotopic Td (assuming an eyelid transmission of 1%).

The masks will be pre-programmed to function only between specific hours, that is, 8 pm to 8 am, to prevent misuse. Outside of these hours, they will not illuminate if worn. The mask is activated when a touch sensor on the device is gently covered with a finger for 3 seconds. It will deactivate if not worn continuously for the first 15 minutes, and after that, the light will remain on for the remainder of the 8-hour period.

Treatment acceptability will be evaluated during a monthly interview with the study investigator. Compliance data will be obtained at the monthly visit from the treatment group both (i) through evaluation of a diary of mask usage, and (ii) objectively through data collected on a chip in the mask itself (based on a sensor which logs when the mask is in contact with the face). This provides precise data on the hours the mask is worn each night by each participant. As each mask is programmed with the unique participant identification code, compliance data stored on-chip will be non-identifiable except via the password-protected electronic database.

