### Masking

It is not appropriate in this study to use a sham treatment, since a non-illuminated mask may have a physiological effect on the retina and patients would be aware that they weren’t perceiving light and so would be unmasked to their intervention group. The study investigator who collects the outcome data will also be providing the masks and instructions on its usage and, hence, will not be masked to the intervention group. However, the potential for experimenter bias is limited, as the primary outcome measure, disease progression, is an objective measurement carried out by automated computer software. The ophthalmologists who are seeing the participants for their regular ranibizumab injections will be masked, which will prevent any bias in their retreatment decisions for the fellow eye.

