### Safety monitoring

All adverse events (AEs) and serious adverse events (SAEs) will be recorded. The chief investigator (AB) will be provided with an update of AEs every month and all SAEs within two working days. This trial does not involve a medicinal product or life-threatening procedure. Hence, the risk of a SAE is low. However, one potential SAE is an increased rate of progression to nAMD in the eye with early AMD at baseline. Although this is at odds with the literature, it is not an impossible outcome. Another potential SAE would be an increased rate of recurrence of nAMD in the fellow eye (resulting in increased ranibizumab retreatment rates). Conversion to nAMD and Ranibizumab retreatment requirement in the fellow eye will be determined by ophthalmologists at the monthly ranibizumab clinic, and recorded by the study investigator through assessment of medical records after each monthly ranibizumab appointment.

Wong et al. [52] carried out a meta-analysis of studies, which had looked at the progression to choroidal neovascularization in the fellow eye when free of advanced disease at study inception. They reported that the cumulative 1-year incidence of nAMD in the 426 patients enrolled in the five studies that evaluated this outcome was 12.2% (confidence interval, 1.7% to 30.6%). Therefore, we have placed an upper limit on the number of people expected to convert to nAMD per month of *n* × (30.6% / 12 months), where *n* is the number of people in the trial who are using the light therapy light mask.

The chief investigator will assess the nature of the AEs and SAEs for seriousness, causality and expectedness. Following the initial report, follow-up data may be requested by the chief investigator. Where the SAE is both related and unexpected, the chief investigator will notify the Trial Steering Committee, the trial sponsor, the National Research Ethics Service North West, and the device manufacturer, who will notify the Medicines and Healthcare Regulatory Agency within 15 days of receiving notification of the SAE.

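### Only the mask arm has a monthly acceptability interview, so participant-reported non-serious adverse events are likely to be recorded more often there, in an unmasked trial with safety as a main aim

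*Protocol article*

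**What the plan says.** The protocol article makes safety a principal purpose. Under Trial objectives it states: "A further main aim of this trial is to assess safety of the mask in the cohort of participants with AMD". Under Safety monitoring: "All adverse events (AEs) and serious adverse events (SAEs) will be recorded".

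The Monthly assessment text in Data collection methods describes a short appointment for both arms, "during which both groups will complete the PSQI sleep quality questionnaire". Trial objectives adds that the PSQI is done "every month with both intervention arms by interview with the study investigator", so controls also have a face-to-face contact each month.

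The same Monthly assessment text then lists items for the mask arm only: download of compliance data, retraining if needed, a check that the mask works, replacement of the mask every 12 weeks, and "a semistructured interview to be carried out to determine the acceptability of the intervention". The Interventions section adds that compliance in this arm is also assessed "through evaluation of a diary of mask usage".

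On masking, the abstract says that "participants will be aware of their treatment group". The Masking section says that the investigator who collects outcome data and hands out the masks "will not be masked to the intervention group".

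**The concern.** How often a minor complaint is recorded depends on how often, and how directly, people are asked. Here one arm has a monthly conversation about living with the device, and the other has no counterpart to it. The participant and the person who writes down the answer both know the allocation. Since every adverse event is to be recorded, a complaint that surfaces in the acceptability interview and qualifies as an adverse event enters the mask arm's count. A control with the same complaint has fewer prompts to mention it.

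The likely direction is towards more recorded events with the mask. The cost runs two ways. An apparent excess of minor events could be an artefact of asking, and a real excess could be dismissed as one. In a Phase I/IIa trial meant to inform a Phase III trial, either would weaken the safety message carried forward.

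**Working it through.** The article gives no figure for adverse event detection, so there is nothing of the plan's own to reproduce on this point. The check compares the routes by which each kind of event can be recorded, and then illustrates the possible size.

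**Routes by arm**

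| Kind of event | Mask arm | Control arm | Same in both arms? |
|---|---|---|---|
| Conversion to nAMD in the early-AMD eye | Clinic ophthalmologist (masked), monthly record review | Same | Yes |
| Ranibizumab retreatment in the fellow eye | Clinic ophthalmologist (masked), monthly record review | Same | Yes |
| Sleep problems | Monthly PSQI by interview | Same | Yes |
| Other participant-reported complaints (eye, skin, headache) | Monthly visit with the investigator, plus acceptability interview, device check and diary review | Monthly visit with the investigator | No |

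The first two rows rest on the Masking, Monthly assessment and Safety monitoring sections, the third on Trial objectives and Monthly assessment. Only the fourth row is unequal. Record review covers both arms, but the article describes it for conversion and retreatment, and minor complaints may never reach eye-clinic notes.

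**Illustration of size**

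Input from the article: 60 participants randomised 1:1, so 60 / 2 = 30 per arm. Assumed inputs, not in the article: the same true risk of a minor event in both arms (20% or 40%), detection of 90% in the mask arm, and detection of 90%, 70% or 50% in controls.

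Recorded risk = true risk × detection probability. Expected participants with a recorded event = 30 × recorded risk. The recorded risk ratio is the ratio of the two detection probabilities, because the true risk cancels.

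True risk 40%, mask arm: 0.40 × 0.90 = 36%, or 10.8 of 30.

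| Control detection | Control recorded risk | Spurious excess | Expected participants, mask v control | Ratio |
|---|---|---|---|---|
| 90% | 0.40 × 0.90 = 36% | 0 points | 10.8 v 10.8 | 1.0 |
| 70% | 0.40 × 0.70 = 28% | 8 points | 10.8 v 8.4 | 1.29 |
| 50% | 0.40 × 0.50 = 20% | 16 points | 10.8 v 6.0 | 1.8 |

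True risk 20%: the mask arm records 0.20 × 0.90 = 18%. Controls record 18%, 14% or 10%, an excess of 0, 4 or 8 points (5.4 v 5.4, 5.4 v 4.2 or 5.4 v 3.0 participants).

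The excess in points therefore depends on both the true risk and the detection gap, and is zero if detection is equal.

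**The case against.** The strongest case against has five parts.

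- **The named safety events are protected.** Conversion and retreatment are judged by masked ophthalmologists and collected by record review in everyone. The numerical safety limit compares mask-arm conversions with an external rate, not with control counts. This stands in full. A reader might infer that the whole safety comparison is biased, or that the control arm is of no use for safety; the article does not support either inference.
- **Controls are not left unasked.** They meet the same investigator monthly and answer the PSQI by interview. This stands, and it narrows the gap in detection. It does not close it, because the PSQI asks about sleep and not about eyes, skin or headache.
- **The interview and diary are not safety instruments.** The interview is semistructured and concerns acceptability, the diary records use, and the article assigns the monthly data to the acceptability and sleep objectives. This stands as description, and it makes the diary a weak route. A complaint voiced in the interview must still be recorded if it is an adverse event.
- **No formal between-arm test of adverse events is specified.** This is correct. A descriptive table by arm would carry the same bias.
- **The elicitation method may be in the full protocol.** The absence of a scripted question from a condensed article is no fault. The one-sided interview, however, is a stated feature. A common question kept elsewhere would reduce the imbalance, but interview-only events would still add to one arm unless coded by source.

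It is also fair that a device interview cannot sensibly be given to untreated controls. The remedy does not ask for that.

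**Conclusion.** The point holds in a limited form. For participant-reported, mainly non-serious events other than sleep problems, the stated visit content gives the mask arm more chances to have an event recorded, with neither the participant nor the investigator masked. More recorded events in that arm are likely, though not certain. The point does not extend to nAMD conversion, ranibizumab retreatment or sleep.

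The size cannot be derived from the documents. The range of 0 to 16 points rests wholly on an assumed 40% true risk, 90% detection in the mask arm and 50% to 90% in controls. It shows what unequal asking could do and is not an estimate for this trial. The change is a cheap improvement that should be made before data collection, since unequal asking cannot be repaired afterwards.

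**What to change.** At every monthly visit:

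1. Ask both arms one identical scripted adverse event question, alongside the PSQI and before any acceptability interview or diary review.
2. Add a source field to the adverse event form: scripted question, medical records, or mask interview or diary.
3. Base the between-arm adverse event summary on events from the scripted question and from medical records.
4. Still record and report events first raised in the mask interview or diary, but list them separately as mask-arm-only findings.

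If the full protocol already has a common question, only its place in the visit, the source field and the reporting rule need to be confirmed or added.

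The cost is a minute or two per visit, one extra field on the form, and a separate list that cannot be compared between arms. No event is lost from the safety record.

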### Statistical methods

It should be noted that, as a Phase I/IIa proof-of-concept study, this research is designed to assess the acceptability of this therapy for the participants, and to provide preliminary data to support a larger Phase III randomized controlled trial in the future, and so is not powered to detect small effect sizes. To maximize retention, all follow-up visits will be timed to coincide with scheduled appointments at the nAMD clinic. We will aim to recruit 60 people, which, allowing for 15% dropout through the year, should leave a final cohort of 51. This will be sufficient to detect a 50% reduction in people showing progression at a probability level of 0.2, with a power of 80%, and a change in the time constant of cone adaptation of 1 minute to be detected at a probability level of 0.05, with a power of 80%. The additional 40 participants enrolled into the cross-sectional part of the study will allow a total cohort of *n* = 100 to address secondary aim 4.

Analysis will be carried out on an intention-to-treat basis. There will be no interim analysis, but conversions to nAMD in the eye with early AMD at baseline, and ranibizumab retreatments for the fellow eye, will be recorded at each participant visit to the nAMD clinic for safety monitoring purposes.

This trial will primarily be concerned with providing information about the safety of the device in the treatment of AMD, and the magnitude of any treatment effect. On this basis, descriptive statistics will be carried out to summarize the demographic characteristics of the two groups, as well as the proportion of individuals showing disease progression in each group, the magnitude of changes in secondary outcome measures, including drusen volume, measures of visual function, and the self-report tests, and the fellow eye retreatment rates.

The primary outcome measure will be the proportion of patients demonstrating disease progression at 12 months. Comparisons will be performed using stratified Mantel-Haenszel tests and presented as forest plots.

Formal statistical analysis will also include linear regression analysis to investigate changes in drusen volume controlling for intervention arm, baseline drusen volume and patient characteristics (such as age, vitamin supplement intake and history of smoking). Analysis of covariance (ANCOVA) will be carried out to compare the change in secondary outcome measures (for example, drusen volume, functional tests, self-report measures) and the ranibizumab retreatment rates over 12 months between the two intervention arms, controlling for the characteristics listed previously. Note that all analysis except for the ranibizumab retreatment rate pertains to the eye with early AMD. This will address secondary aim 1. To meet our fourth secondary aim, which is to establish the relationship between baseline functional biomarker outcomes and the severity of AMD, we will carry out a one-way analysis of variance (ANOVA) to compare the mean results at baseline between participants with grades of AMD in each group on the AREDS simplified scale. This analysis will take place when the baseline data collection is complete. To assess the ability of the clinical tests to act as prognostic and predictive biomarkers, receiver operating characteristics curves will be constructed to plot the sensitivity and specificity of the baseline measures in predicting outcomes within the control and intervention arms, respectively. This will address secondary aims 5 and 6. When the trial is completed, linear regression analysis will be used to determine how well the change in the functional measures relate to the change in our primary outcome measure (drusen volume), which is a validated biomarker for disease progression. This will address the seventh secondary aim.

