### Randomization

Participants will be stratified according to risk of AMD progression (using the AREDS simplified scale [45]), and randomly allocated to receive either the light mask or no intervention in a 1:1 ratio using computer-generated random permuted blocks (both groups will continue to receive ranibizumab injections as required for the fellow eye). The study investigator will be provided with three piles of envelopes by the chief investigator, in order to randomize the participant to either the intervention or control arm of the study. Each pile relates to a different stratum of randomization, that is, grade 2, 3 or 4 of AMD, according to the AREDS simplified scale. The envelopes in each pile will be numbered, and will contain the randomization allocation for each participant.

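### The ANCOVA of change in functional and self-report outcomes names neither each outcome's own baseline nor the AREDS randomisation stratum, which gives up some precision

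*Protocol article*

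**What the plan says.** Three parts of the protocol article bear on this.

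- **Statistical methods, drusen regression.** Change in drusen volume is regressed "controlling for intervention arm, baseline drusen volume and patient characteristics (such as age, vitamin supplement intake and history of smoking"). The bracketed list is introduced as examples, so it is open.
- **Statistical methods, ANCOVA.** A further analysis will "compare the change in secondary outcome measures (for example, drusen volume, functional tests, self-report measures"), and also retreatment rates, "between the two intervention arms, controlling for the characteristics listed previously". No separate covariate list is given for the functional or self-report outcomes.
- **Randomization.** "Participants will be stratified according to risk of AMD progression", in three strata: AREDS simplified scale grades 2, 3 and 4.

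The only stratified method is for the binary progression outcome: "Comparisons will be performed using stratified Mantel-Haenszel tests and presented as forest plots". The strata are not named there.

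The data needed for fuller adjustment are collected. Under Data collection methods, the questionnaires are completed at screening, and the functional tests and AREDS grading are done at baseline. For the 12-month visit, "This visit will be the same as the baseline visit with the addition of a final semistructured interview" and the questionnaires.

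**The concern.** For acuity, chromatic threshold, flicker threshold and the questionnaires, the baseline value of the same measure will usually be the strongest predictor of the 12-month value. It is not named. The cross-reference supplies either the baseline of a different variable (drusen volume) or, if only patient characteristics are carried over, no baseline at all. The stratification factor is not named either, although an analysis that follows the randomisation would normally include it.

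The trial says its main concerns are safety and the size of any treatment effect, as groundwork for a Phase III trial. With about 51 participants analysed, avoidable variance in the effect estimates is a real cost. So is an estimate that moves with whatever baseline difference the randomisation happens to produce.

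**Working it through.** **1. The plan's own figures.** 60 × (1 − 0.15) = 51, or 25.5 per arm at 1:1. For 60% against 30% progression at two-sided 0.2, the power with 25.5 per arm is 0.82, against the 80% stated. The sample size reproduces, and the point made here changes none of these figures.

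**2. What the cross-reference supplies.**

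| Reading of the cross-reference | Drusen baseline carried over | Own baseline of functional or self-report outcome | AREDS grade |
|---|---|---|---|
| Whole list | yes | not named | not named |
| Patient characteristics only | no | not named | not named, but the list is open |

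Own baseline is missing on both literal readings.

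**3. Variance, closed form.** Let ρ be the correlation between baseline and 12-month values. It is an assumption, since the documents give none. With equal variances σ² at both times:

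- the variance of an unadjusted change score is proportional to 2σ²(1 − ρ);
- after adjustment for own baseline it is proportional to σ²(1 − ρ²);
- the ratio, adjusted to unadjusted, is (1 − ρ²) / [2(1 − ρ)] = (1 + ρ)/2.

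| ρ (assumed) | Variance ratio (1 + ρ)/2 | Variance cut | Excess SE without own baseline, 1/√ratio − 1 | 51 unadjusted participants are worth (51 × ratio) |
|---|---|---|---|---|
| 0.5 | 0.75 | 25% | 15.5% | 38 |
| 0.7 | 0.85 | 15% | 8.5% | 43 |
| 0.9 | 0.95 | 5% | 2.6% | 48 |

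**4. Chance imbalance.** The SE of the baseline difference between arms is √(2/25.5) = 0.28 SD. An unadjusted change score carries −(1 − ρ) times that difference into the estimate. A one-SE imbalance therefore shifts it by 0.5 × 0.28 = 0.14 SD, 0.3 × 0.28 = 0.08 SD or 0.1 × 0.28 = 0.03 SD. This is the mechanism behind the variance in step 3, seen for a single randomisation. It is not a second cost to be added.

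**5. Closer to the planned model.** Step 3 compares with a wholly unadjusted change score, but the plan does adjust for something. A simulation (51 participants, 4,000 runs per setting) put baseline drusen volume, age, smoking and supplement use in both models and added own baseline to one. Drusen volume was correlated 0 or 0.3 with the outcome's baseline. The other three covariates were generated as unrelated to the outcome.

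| ρ | Variance ratio, drusen correlation 0 | Variance ratio, drusen correlation 0.3 | Variance cut |
|---|---|---|---|
| 0.5 | 0.785 | 0.773 | 21-23% |
| 0.7 | 0.870 | 0.888 | 11-13% |
| 0.9 | 0.985 | 0.970 | 2-3% |

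Baseline drusen volume does not make up the loss in these settings. The mean estimate was within about 0.01 SD of zero in every setting, with and without own baseline, so no systematic bias appeared.

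**6. Stratum.** The document gives nothing that relates AREDS grade to the functional or self-report outcomes, so the gain cannot be computed.

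**The case against.** The strongest reply is that this is a condensed article. Its covariate list is open, and the per-outcome lists may be settled in a statistical analysis plan that is not shown. For AREDS grade this has force: as a prognostic factor it could be meant among the patient characteristics, and baseline drusen volume may partly stand in for it. What stands is that grade is not named, not that it is excluded. For own baseline the reply is weaker, because the baseline of a functional test or questionnaire is not naturally a patient characteristic. One could also argue that the drusen regression, which does adjust for its own baseline, sets a pattern for the ANCOVA to follow. The wording does not say so. Calling the method ANCOVA does not supply the covariate either, since the text states what is controlled for.

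A reader might also infer stronger points that the document does not support:

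- **That the arm difference is biased by regression to the mean.** Under randomisation both arms regress equally in expectation. The harm is lost precision and conditional imbalance.
- **That a co-primary analysis is defective.** Retinal adaptation is co-primary, and the ANCOVA is stated for secondary outcomes. It may be meant among the functional tests, but the text does not say so.
- **That the loss is always material.** At ρ = 0.9 it is 2-5% of the variance, which is negligible.
- **That the same point covers retreatments.** Own-baseline adjustment does not bear on them. How to model them is a separate question, with no size established here.

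**Conclusion.** The point holds as an improvement to the stated covariate set. As written, the change scores for functional and self-report outcomes are not adjusted for their own baselines, and AREDS grade is named in no regression or ANCOVA. Under the assumed correlations of 0.5 to 0.9, own-baseline adjustment lowers the variance by 25% to 5% against an unadjusted change score, and by about 23% to 2% with the listed covariates in both models. The gain from the stratum is unknown. Leaving the stratum out would tend to overstate standard errors, which is the conservative direction. The stratified analysis of the progression outcome and the sample size are untouched. The size rests entirely on ρ, which should be replaced by repeatability or pilot data if the investigators have them.

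**What to change.** - For each continuous functional and self-report outcome, state that the 12-month value (or the change) is modelled on arm, that outcome's own baseline and AREDS stratum (2/3/4). Age, smoking and supplement use can stay as further covariates if wanted, as a short fixed list.
- Add AREDS stratum to the drusen volume regression, which already has its own baseline.
- Say whether retinal adaptation is analysed by this ANCOVA. If it is, use the same model.

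The cost is one degree of freedom for own baseline and two for a three-level stratum, so about three. The model in the simulation without own baseline has six coefficients (intercept, arm, drusen baseline, age, smoking, supplements), leaving 51 − 6 = 45 residual degrees of freedom. Three more leave 42. The change is to analysis wording only, because all the variables are already collected. Fixing the list before the data are seen also removes a later choice of covariates in an open-label trial.
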